# Protocol for the Work Engagement and Well-being Study (SWELL): a randomised controlled feasibility trial evaluating the effects of mindfulness versus light physical exercise at work

**DOI:** 10.1136/bmjopen-2021-050951

**Published:** 2022-04-11

**Keywords:** PUBLIC HEALTH, PREVENTIVE MEDICINE, OCCUPATIONAL & INDUSTRIAL MEDICINE

## Abstract

**Introduction:**

Mental ill health is a major cause of disability. Workplaces are attractive for preventative interventions since most adults work; meanwhile, employers are interested in improving employees’ well-being and productivity. Mindfulness-based programmes are increasingly popular in occupational settings. However, there is inconsistent evidence whether mindfulness interventions improve work performance and how effective mindfulness-based programmes are, compared with other interventions, in preventing mental ill health.

**Methods and analysis:**

In this online randomised controlled feasibility trial, an anticipated 240 employees will be randomised to either a 4-week light physical exercise course or a mindfulness course of the same duration (1:1 allocation). The primary outcome is work performance, measured using the Work Role Functioning Questionnaire. We aim to evaluate the acceptability, feasibility and procedural uncertainties of a randomised controlled trial in a workplace, calculate an effect size estimate to inform power calculations for a larger trial, and explore whether improved executive function and/or enhanced mental health could be potential mechanisms underlying the effect of mindfulness on work performance. Outcomes will be collected at baseline, postintervention and 12-week follow-up.

**Ethics and dissemination:**

Approval has been obtained from Cambridge Psychology Research Ethics Committee. (PRE.2020072). Results will be published in peer-reviewed journals. A lay summary will be disseminated to a wider audience including participating employers.

**Trial registration number:**

NCT04631302.

Strengths and limitations of this studyA randomised controlled trial to lay the foundations to investigate the mechanisms of mindfulness intervention underlying effects on work performance.The study employs a range of outcome measures, including self-reported measures and cognitive functioning tasks.This feasibility trial is not powered to detect significant effects, but rather to estimate effect size to inform design of a larger later-stage trial.Several feasibility outcomes will be collected to inform a later-stage trial.

## Introduction

### Background and rationale

Mental illness is a major cause of disability worldwide.^1^ Much of the adult population is employed and spends about a third of their waking hours doing paid work.^2 3^ The occupational environment is therefore an opportune setting for preventative mental health interventions.

Poor mental health is responsible for 44% of work-related episodes of ill health^4^ and according to conservative estimates, is thought to cost the UK’s economy £45 billion annually^5^ or 2% of UK’s Gross Domestic Product. To reduce this burden, a growing number of employers provide programmes to improve well-being and work performance.

Mindfulness-based programmes (MBPs) are increasingly popular at places of work. Mindfulness is typically defined as ‘the awareness that emerges through paying attention on purpose, in the present moment and non-judgementally to the unfolding of experience moment by moment’.^6^ Practising such awareness is linked to reduction in symptoms of anxiety, depression and stress in community populations.^7 8^ There is also evidence that mindfulness training could improve overall well-being,^8 9^ life satisfaction^10^ and quality of life.^7^

Mindfulness practice may yield workplace benefits beyond emotional well-being. It has been proposed that mindfulness improves work performance^11^ and reduces the negative effects of multitasking.^12^ Yet, there is little evidence to support these claims. A recent meta-analysis concluded that work performance was rarely assessed in trials investigating the outcomes of MBPs.^13^ When work performance was measured, wide-ranging operational definitions were used, for example, engagement,^14–18^ motivation,^15^ absenteeism^19^ and presenteeism,^17–19^ rate of errors^20^ and burn-out.^21^ Thus, estimating an overall effect is difficult.^13 22^ Methods for measuring performance in higher education have less variability, yet there is no clear indication that offering mindfulness training to university students improves their academic performance.^23^

The mechanisms underlying any effect of mindfulness on work performance are also yet to be determined while two mechanistic pathways stand out that could explain such an effect of MBPs. First, positive effects of MBPs on mental well-being are well established,^7–9^ and mental well-being is linked to better work performance.^24 25^ Conversely, mental health problems decrease employees’ performance,^26–28^ particularly if these problems are poorly managed.^29^ However, an indirect effect of MBPs on workplace performance via improved mental well-being has yet to be evaluated.

A second potential mechanism could be an improved cognitive control over mental activity, which allows one to prioritise current task-relevant goals.^30 31^ There are three potential facets of cognitive control that may be improved by MBPs: (1) shifting, that is, the ability to switch between multiple tasks; (2) updating, or the ability to frequently refresh information in working memory to ensure a currently relevant record of information and (3) inhibition: deliberately hindering dominant or automatic responses that are irrelevant to the task at hand.^32^ Improved cognitive control, in turn, may lead to better performance on workplace tasks.^11 33^

Mindfulness has been shown to have a small effect on cognitive control.^34 35^ A recent meta-analysis analysing outcomes of randomised controlled trials (RCTs) measuring the effects of cognitive control in MBPs for healthy participants found a small overall effect of Hedge’s *g*=0.2.^35^ However, we know little about how these changes in cognitive control manifest in the workplace.^13^ While mindfulness may improve performance on tasks closely related to the practice, such as counting breaths,^36^ it may not extend to other tasks, such as those completed at work.^37^

Furthermore, to date, research has primarily focused on the impact of mindfulness on cognitive control over emotionally neutral information. Yet, much of the everyday mental activity that we seek to regulate is emotionally positive or negative.^38 39^ In the two meta-analysis of MBPs’ effects on cognitive control published to date,^34 35^ only one identified study used emotional stimuli within an cognitive control task. This study reported a null-effect of meditation on cognitive control measured via an attention network test when comparing negative and neutral conditions.^40^ It is important to note that this study^40^ was likely underpowered.

At work, it is arguably beneficial to inhibit emotional thoughts (eg, worrying about a recent argument with your spouse) that are irrelevant to the task at hand (eg, writing a report). A reduced ability to inhibit internal emotional stimuli may interfere with our ability to maintain focus on workplace tasks. There is evidence that emotional stimuli inhibit cognitive control, when measured using the Stop-Signal Task.^41–43^ As mindful meditation trains the ability to move away from thoughts and images of negative emotional valence, practising mindfulness may enhance cognitive control over emotional mental events.^44^ It is therefore important to determine whether MBPs improve workplace performance via enhancement of cognitive control skills such as the ability to move away from negative stimuli (eg, worries about task performance) or to decentre from negative mental content^45 46^ and refocus attention on the task at hand.^22^

Understanding the mechanisms underlying effects of MBPs on work performance would (1) help to design more targeted interventions, (2) improve our attempts to assess MBPs, by designing and selecting more stringent outcome measures and control interventions and (3) inform an understanding of for whom MBPs may be most effective, and in which context.^47^

### Objectives

Current literature suggests that MBPs could improve work performance through increased mental well-being and/or cognitive control over emotional material. In order to test this, we need to control for one of the two pathways. Both the MBP and light exercise have been shown to reduce stress, depression and anxiety,^48–50^ however, only mindfulness is expected to improve cognitive control skills. We chose light exercises as a condition to help to distinguish between the different pathways through which work performance may improve.

A definitive RCT is needed to evaluate these potential mechanisms. However, methodological uncertainties and questions of acceptability and feasibility need clarification to inform the design of such a trial.^51–53^ We aim to conduct a feasibility trial to clarify these uncertainties and complete a preliminary investigation of the relationships between mindfulness training, workplace performance and the proposed mechanisms of action.

This feasibility trial will:

Estimate the between-groups effect size for the effect of mindfulness, relative to a light exercise control condition, on our primary outcome of work performance, in order to inform power calculation for a larger trial.Explore whether improved cognitive control and/or enhanced mental health could be potential mechanisms underlying the effect of mindfulness on work performance.Assess the acceptability of the interventions and the study design by monitoring recruitment, retention and adherence to the course.Determine procedural feasibility of a later stage trial by evaluating the willingness of the participants to be randomised and other practical implications of running a RCT at a workplace.

## Methods

This protocol follows the guidelines for RCTs set by the Standard Protocol Items: Recommendations for Interventional Trials (SPIRIT) 2013 statement^54^ (SPIRIT checklist in online supplemental file 1). Initial consent taking started in November 2020. Participants, irrespective of the time they consent, received access to baseline measures from 23 February 2021. Data collection finished on 23 March 2022.

10.1136/bmjopen-2021-050951.supp1Supplementary data

### Study design

This is a participant-level RCT. Employees will be randomly allocated in a 1:1 ratio to either of two parallel groups.

### Eligibility criteria

Eligibility to participate in this study will be self-reported. The employers who have agreed to participate in the study are local councils or education providers or trade either in the publishing, electronics or construction industry with employees in a variety of roles, mostly in desk-based occupations. Individuals can participate if they work for the employers taking part in this trial, are based in the UK, and are not currently on a long-term leave. We will recommend that a participant chooses not to join the study if they:

Are currently suffering from severe periods of anxiety, depression or hypomania/mania.Are experiencing other severe mental illnesses.Have had a recent bereavement or major loss.Have already completed a mindfulness course or have meditated more than 10 hours in the past 10 years.

### Intervention condition: *Be Mindful* MBP

Participants in the Mindfulness condition will complete the *Be Mindful* prerecorded online course by Wellmind Media. It incorporates elements from Mindfulness-Based Stress Reduction^55^ and Mindfulness-Based Cognitive Therapy.^56^ Course materials and instructional videos are accessed through a website (http://www.bemindfulonline.com).

The 4-week course consists of 10 sessions led by 2 teachers, 1 female, 1 male. Participants are taught to use formal meditations (focusing attention on the practice of meditation) as well as informal mindfulness techniques, such as mindful walking and mindful eating. Daily homework includes a formal mediation practice with the assistance of video/audiorecordings (up to 30 min), and one or two informal exercises per day (see table 1 for an overview). Every week, participants receive emails motivating them to practice and informing them when the next module is available. As this is a feasibility examination for a pragmatic trial, no modifications to the procedures to maintain adherence to the intervention will be implemented.

**Table 1 T1:** Comparison of the intervention and control group

Condition	Intervention: be mindful	Control: light physical exercise
No of sessions in total	10	28
Online coursework frequency	Twice weekly	Daily
Typical session and its length	Self-paced. Includes videos (average of 3–4 min in total per session), self-reflection exercises and brief reading tasks.	Videos of 10–13 min.
Homework frequency	Daily	Daily
Typical assignment	A formal meditation (10–30 min) and shorter task such as journaling or noticing. The frequency of the latter varies from daily to once a week.	Using the exercises while taking brief breaks during the day.
Reminders to encourage practising	Four times a week	Four times a week

### Control condition: light physical exercise

The 4-week control condition involves light exercises aimed at increasing mobility, reducing stiffness, improving blood circulation, and avoiding pain or repetitive strain injuries that may result from sedentary or repetitive tasks common in office environments. The prerecorded exercises will include whole-body slightly aerobic exercises such as rotation of joints and stretching. This online course was developed by JG, a public health doctor, together with an expert in body posture.

The control condition course is designed to match the intervention condition in overall time commitment, and the frequency of interaction with the participant (see table 1). It replicates the encouraged use of short breaks throughout the workday to focus on well-being, as in the intervention condition.

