#### Primary outcome: work performance

Work performance will be measured by using the 25-item Work Role Functioning Questionnaire’s (WRFQ) 57 updated version,^58^ to capture perceived difficulties in meeting work demands. Items are rated on a 5-point scale (‘difficult all the time’ to ’difficult none of the time’), with higher scores indicating better functioning. A sixth option denotes ‘does not apply to my job’. The questionnaire has not been validated in English. Validations completed in Dutch,^58^ Spanish,^59^ and Norwegian^60^ have shown good internal consistency (Cronbach alphas (α) 0.7–0.9),^58–60^ and test-retest reliability (ICC=0.66, 95% CI 0.54 to 0.76 for the total score).^58^ The WRFQ features four subscales: work scheduling and output demands (α=0.92), physical demands (α=0.92), mental and social demands (α=0.91), and flexibility demands (α=0.96).^58^ The WRFQ has been shown to possess decent convergent validity, correlating with similar measures including the Utrecht Work Engagement Scale^61^ (r=0.304),^58^ Work Ability Index^62^ (r=0.468).^58^ The primary endpoint in this trial will be the postintervention measurement. Feasibility of using the 12 week follow-up as the main outcome end-point in the later-stage trial, will be assessed. We recognise that effects at 12 weeks may not be sustained longer term. Retention at 12 weeks will help to plan the sample size for a larger trial which could also then measure outcomes longer term.

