### Statistical methods

Central tendencies, dispersion and data missingness will be reported for all time points. At baseline, descriptive statistics will be presented overall and by group allocation. At following timepoints, outcomes will be reported by group.

Any significance testing, though not the focus of this trial, will follow the intention-to-treat principle. A key limitation of feasibility trials such as this is that adequate power is not obtained to detect statistical significance. For the primary outcome, a linear multiple regression model will compare the WRFQ total score between trial arms at postintervention, adjusted for baseline WRFQ and employer. Multiple imputation will be used to account for missing data. Further exploratory analysis will employ the same approach for other outcome measures at postintervention and 12-week follow-up. Mediation analysis techniques will be employed to assess the suggested mechanistic pathways. Effect sizes obtained in these analyses will be used to inform a potential later-stage trial and are the focus of this trial, rather than statistical significance.

For the secondary outcomes, mixed model repeated measures analysis will be performed using the daily monitoring of work performance to study changes between arms during the intervention. The analysis will also compare different work performance measures. Again, the focus of this trial is on obtaining an estimate of likely effect sizes, rather than statistical significance.

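### The exercise control may improve physical work functioning, which the WRFQ total scores, so the total-score contrast alone does not isolate cognitive control

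*Protocol article*

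**What the plan says.** The Objectives section names two routes to better work performance, mental well-being and cognitive control, and then sets the condition for telling them apart: "In order to test this, we need to control for one of the two pathways". Both courses are said to reduce stress, depression and anxiety, while "only mindfulness is expected to improve cognitive control skills". Hence the choice of comparator: "We chose light exercises as a condition to help to distinguish between the different pathways through which work performance may improve".

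The section on the control condition describes the course as "light exercises aimed at increasing mobility, reducing stiffness, improving blood circulation, and avoiding pain or repetitive strain injuries", with office work in mind.

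The primary outcome section says that the 25-item WRFQ is used "to capture perceived difficulties in meeting work demands" and lists its parts: "The WRFQ features four subscales: work scheduling and output demands (α=0.92), physical demands (α=0.92), mental and social demands", followed by flexibility demands. Under Statistical methods, "a linear multiple regression model will compare the WRFQ total score between trial arms at postintervention", adjusted for baseline WRFQ and employer. The same section plans mediation analysis of the suggested pathways and says that effect sizes are the focus and will inform a later trial.

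**The concern.** The reasoning in the Objectives works only if exercise reaches work performance through mental health alone. The description of the control course gives it a further declared aim, physical function, and the primary score counts physical demands. The Objectives do not mention this route, and no outcome in the protocol is set up as a mediator for it.

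What is at stake is objective 2, the exploration of mechanisms. A real cognitive-control benefit could be partly or wholly offset in the total by a physical gain in the exercise arm. Someone reading the total-score difference through the two-pathway reasoning would then conclude wrongly that the cognitive pathway is absent.

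**Working it through.** **1. The contrast.** Let M be the mental-health effect shared by both courses, C the cognitive-control effect of mindfulness, and P any physical benefit of exercise that the WRFQ registers.

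- As reasoned in the Objectives: (M + C) − M = C.
- With the control course as described: (M + C) − (M + P) = C − P.

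A difference near zero is compatible with C = 0 and P = 0, and equally with C = P > 0.

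**2. Does the outcome register P?** Yes. Physical demands is one of four subscales, and the planned model uses the total.

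**3. Is P measured as a pathway?** Cognitive control, well-being, stress, depression and anxiety are measured directly. Physical health appears as a possible baseline covariate and in an item on health conditions that affect ability to work, but not as a mediator. In the mediation analysis P therefore enters the direct effect with a negative sign.

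**4. Precision available.** The plan's completer figures reproduce: 240 × (1 − 0.47) = 127.2, stated as 128 (64 per arm); and 128 × 0.53 = 67.8, stated as 68. No stated figure is in dispute. With 64 per arm, the unadjusted 95% half-width for a standardised difference is 1.96 × √(2/64) = 0.35 SD.

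**5. Illustrative size.** The documents give no item count for the subscale, no correlation between subscales and no expected physical effect. All of the following are assumptions:

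- w, weight of the physical items in the total: 0.16 to 0.25 (central 0.20)
- ρ, correlation between physical and other items: 0.3 to 0.6
- dp, gain on physical items from exercise: 0.2 to 0.4 SD (central 0.3)
- benefit of mindfulness: 0.20 SD, borrowed from the Hedges g for cognitive control in the Background; it is not a WRFQ figure

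Total = w × physical + (1 − w) × other, each part with SD 1, so the SD of the total is D = √(w² + (1 − w)² + 2w(1 − w)ρ). At w = 0.20, D = 0.881 (ρ = 0.3) or 0.934 (ρ = 0.6).

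Offset due to exercise alone = w × dp / D. The central case is 0.06/0.934 to 0.06/0.881 = 0.064 to 0.068 SD. The full range is 0.034 to 0.116 SD.

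Net effect on the total in the central case, with n per arm = 2 × ((1.96 + 0.842)/d)², rounded up (80% power, two-sided 5%):

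| Mindfulness acts on | No exercise effect (dp = 0) | Exercise effect dp = 0.3 |
|---|---|---|
| Non-physical items only | 0.16/D = 0.171–0.182; n = 476–535 | 0.10/D = 0.107–0.114; n = 1,219–1,369 |
| All items equally | 0.20/D = 0.214–0.227; n = 305–343 | 0.14/D = 0.150–0.159; n = 622–699 |

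In the first row, the step from 0.20 to 0.171–0.182 is dilution, because mindfulness is assumed not to move the physical items. It is not caused by the control course. If dp is instead expressed in SDs of the total, the net effect is 0.20 − 0.20 × 0.3 = 0.14, with n = 801 against 393 at 0.20. For w = 0.1 to 0.3 and dp = 0.1 to 0.5 on that scale, the offset is 0.01 to 0.15 SD.

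The same central inputs thus give 622 to 1,369 per arm depending on how they are modelled. Only the direction of the offset follows from the text. Every offset shown is well inside the 0.35 SD half-width, so the total alone could not reveal it.

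**The case against.** **Objective 1.** It asks for the effect of mindfulness relative to a light exercise control, to inform the power of a larger trial. That estimand includes everything exercise does. A reader might infer that the effect size carried forward is therefore wrong. The documents do not support this. For a later trial with the same comparator and the WRFQ total, the net effect is the right planning figure, and sizing such a trial on a larger effect without the physical items would underpower it. This part of the objection stands in full.

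**Mediation.** A reader might also infer that the trial cannot separate its two pathways at all. That goes too far. The protocol assigns the pathways to mediation analysis with directly measured mediators, and a physical route in the direct effect does not by itself erase the indirect effects. The Objectives claim only that exercise will help to distinguish the pathways, and objective 2 is exploratory.

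**Size.** The exercises are light and last four weeks, part of their aim is preventive, staff are mostly desk-based, and WRFQ items can be marked as not applicable to the job. Physical items may sit near ceiling and the offset may be small. This stands.

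**Already covered, or left to the analysis plan.** The protocol lists the suitability of its primary measure as an uncertainty, adds other work outcomes and will compare work performance measures. A condensed article may also leave subscale models to an analysis plan that is not shown, so their absence alone is no finding. What remains is a mismatch within the stated text: the two-pathway rationale does not fit the stated aims of the control course together with the stated composition of the primary score.

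**Conclusion.** The point holds for the mechanistic reading of the total-score contrast. That contrast estimates any cognitive-control benefit minus any physical benefit of exercise, so a small or null value is not evidence against the cognitive pathway. The pragmatic comparison of the two courses is unaffected.

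The size is unknown. The 0.03 to 0.12 SD offset rests wholly on assumed weights, correlations and physical gains, and the true value could be close to nil. A negative direct effect in the mediation analysis might be read as harm from mindfulness. The documents give no ground for that, since the direct effect is relative to an active comparator with its own aims. This is a worthwhile, inexpensive improvement to an exploratory feasibility trial, not a flaw in its primary estimate.

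**What to change.** - Keep the WRFQ total at postintervention as the primary outcome, and as the planning effect size for any later trial that uses that total and this comparator.
- Add the same regression (adjusted for baseline and employer) on the WRFQ without the physical-demands subscale, and on that subscale alone.
- Run the mediation analysis on the score without physical demands alongside the total.
- In the Objectives, state that light exercise may also act through physical function, so that the total-score contrast alone does not isolate cognitive control.

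The Methods section reports that data collection has finished. These changes use items already collected and alter neither the control course nor the primary analysis. The cost is a few more reported estimates and a shorter, slightly less reliable score. The reduced score also does not remove every physical influence, since less pain or stiffness could ease other work demands. It removes the most direct one, and the subscale analysis shows whether a physical effect is visible.
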